### Data Monitoring and Management

Data monitoring and management for this study, coordinated by the School of Nursing and Midwifery at the Aga Khan University, with strategic guidance from a steering committee, involves several key roles and processes. Trained psychologists will collect data, while the primary author will oversee data management (entry validation, cleaning, and secure storage) and monitor participant safety during data collection using safeTALK training, with protocols for immediate counselor referrals if distress occurs. A dedicated, separate data analyst will conduct statistical analyses. An independent data monitoring committee, composed of external experts, including clinicians and a biostatistician operating under a charter, will periodically review trial data for safety, efficacy, and overall conduct, managing interim analyses with predefined stopping guidelines and restricted access to results. Comprehensive procedures are in place for managing and reporting adverse events, with investigators responsible for the timely reporting of serious events. Finally, independent personnel will conduct periodic audits, detailed in a separate plan, to ensure trial quality and compliance.

### Ethical Considerations

#### Overview

This research is fundamentally guided by a commitment to ethical principles, ensuring participant protection. This study has received formal approval from the Aga Khan University Ethics Review Committee (AKU-ERC; 2023-8509-24844) and is transparently registered on ClinicalTrials.gov (NCT06721364). Should any significant adjustments to the study protocol arise (such as changes to eligibility, outcomes, or analysis), these will be communicated efficiently to the investigators, AKU-ERC, the trial registry, and other relevant parties (such as participants or journals) using an online portal.

#### Ethics Approval and Consent to Participate

The interventions in this study strictly adhere to the principles and procedures specified in the Declaration of Helsinki. All experimental protocols have been thoroughly reviewed and approved by the AKU-ERC (Multimedia Appendix 1). Informed consent will be obtained from all study participants, ensuring ethical standards are followed throughout the research process. Transportation incentives will be provided for participation.

#### Consent for Publication

Participants will be asked for their consent during the data collection process, explaining that the collected data may be used for the dissemination of scientific knowledge. However, no personal names or specific identifying information will be revealed in the published material to ensure confidentiality and privacy (Multimedia Appendix 2). Participants will also be requested to give permission to publish any relevant data or materials without disclosing their identity.

Participation in this study is entirely voluntary. The research team, composed of psychologists and the principal investigator, will secure informed consent from parents or guardians after clearly explaining the study’s objectives during sessions at the school, allowing ample time for inquiries and ensuring a pressure-free decision environment. Students will provide their own informed assent (Multimedia Appendix 3). It is crucial that participants know they can withdraw from the study at any stage without facing any disadvantage; should they choose to withdraw, their collected information will be removed from the study analysis. Currently, no ancillary studies requiring separate consent for data use are planned.

Maintaining participant confidentiality is a priority throughout the research process—before, during, and after data collection. Personal information will be gathered securely, and anonymity will be protected by using unique identification codes and pseudonyms, effectively separating personal identities from research data. All electronic data files are password protected, and any reports generated will exclude identifying details such as names. While the study presents minimal potential risks, if a participant’s results suggest potential susceptibility, this information will be confidentially discussed with their parents (only after obtaining explicit parental consent) to facilitate a referral for further assessment. This sensitive information will not be disclosed to school authorities. The psychologists assisting with data collection are prepared to identify and offer support for any immediate distress participants might experience.

Access to the final, anonymized dataset is carefully controlled, limited to the primary author, data analyst, principal investigator, and supervising committee members directly involved in data analysis and reporting. Importantly, there are no contractual limitations restricting the investigators’ access to the data. The findings from this research will be shared through various channels, including publications in peer-reviewed journals, presentations at academic conferences, and mandatory reporting on the ClinicalTrials.gov database. In addition, summaries might be shared with participants and other relevant stakeholders when appropriate. Authorship for publications will align with the established International Committee of Medical Journal Editors guidelines. Following the main dissemination of results, the research team will address reasonable requests for access to the complete study protocol, the anonymized participant dataset, and the statistical code used for analysis.

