### Study Outcomes

#### Suicidal Ideation

The level of suicide literacy among the participants will be measured through the MSSI by Miller et al [43], comprising 21 items. It was translated and used in Urdu by Bakht et al [51]. The MSSI has shown strong internal consistency, with a Cronbach α coefficient ranging from 0.87 to 0.94 [52]. The severity of suicidal ideation, as assessed by the MSSI total score, is categorized into 3 levels. A total score ranging from 0 to 8 indicates a low level of suicidal ideation. In contrast, a total score between 9 and 20 suggests a moderate level of suicidal ideation. These adolescents may experience more frequent or persistent thoughts of suicide, potentially accompanied by feelings of hopelessness or despair. Finally, a total score of 21 or higher reflects a severe level of suicidal ideation, indicating a significant risk of self-harm or suicide. Adolescents in this category may have intense and intrusive thoughts of ending their life, and immediate intervention and support are often necessary to ensure their safety. Severe suicidal ideation is indicated by a total MSSI score exceeding 20, coupled with an intense suicidal intention, represented by a score of more than 1 on item 7. In addition, an active desire to make an attempt is signaled by a score exceeding 1 on item 3, while a serious plan for suicide is indicated by a score of more than 1 on item 15.

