### Potential Risk to Participants

This study has minimal potential risks for the participants. While obtaining informed consent from the parents and assent from the participants, it will be made clear that information regarding those considered susceptible, based on their scores, will be shared with their parents, and they will be referred for further assessment after the parents’ consent. However, the status of the participants will be kept confidential from the school authorities. The study will involve psychologists who will conduct the interview along with the principal investigator; hence, they will be able to screen the potential participants.

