### Ancillary and Posttrial Care and Referral Mechanism

The data will be collected by trained psychologists, and all the identified cases will be referred to a counselor who will also be hired for the study, so they can refer the extreme cases for further treatment. The employed counselors will be on hand at the study sites for data collection and intervention. The cases presenting extreme suicidal ideation thoughts will be referred for follow-up. The screening and referral expenses of the participants will be borne by the study [71]. The attendees will also be informed about the resources that are accessible, such as the hotlines of the suicide prevention organizations operating in Pakistan.

For this trial, the criteria for discontinuing or modifying allocated interventions for a participant will include a participant’s explicit request to withdraw, the emergence of any unforeseen serious adverse events related to the intervention, or if the participant’s mental state significantly deteriorates, requiring a different level of care. Strategies to improve adherence to the intervention protocol will involve clear communication of the program’s duration and expectations during the informed consent process; regular engagement with participants, which may include follow-ups; and ensuring the intervention is delivered in a manner that is acceptable and feasible for the participants. Participants will be informed about any permitted or prohibited concomitant care or interventions during the trial period to avoid any potential confounding factors.

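### The consent rules for telling parents conflict, severe ideation has two definitions, and the uncontrolled ideation change cannot be separated from referral

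*Protocol article*

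**What the plan says.** Five sections of the protocol article bear on disclosure, referral and severity.

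- **Consent for Publication** (under Ethical Considerations): if results suggest susceptibility, "this information will be confidentially discussed with their parents (only after obtaining explicit parental consent) to facilitate a referral for further assessment". The condition that matters here is "only after obtaining explicit parental consent".
- **Potential Risk to Participants**: families are told at consent and assent that "information regarding those considered susceptible, based on their scores, will be shared with their parents", and that "they will be referred for further assessment after the parents’ consent".
- **Ancillary and Posttrial Care and Referral Mechanism**: "all the identified cases will be referred to a counselor who will also be hired for the study". The counselor can send extreme cases on for treatment. No consent step is stated.
- **Data Monitoring and Management**: participant safety is monitored during data collection, "with protocols for immediate counselor referrals if distress occurs". Again no consent step is stated.
- **Suicidal Ideation** (under Study Outcomes): "a total score of 21 or higher reflects a severe level of suicidal ideation". Later in the same paragraph: "Severe suicidal ideation is indicated by a total MSSI score exceeding 20, coupled with an intense suicidal intention", the latter meaning more than 1 on item 7.

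For the analysis, Pretest Phase has a psychologist and the researcher assess every student's suicide risk before training. Null Hypotheses compares ideation at baseline and at 8 weeks. Study Design states that there is no control group. Data Analysis models current suicidal ideation as a binary outcome with a generalized estimating equation.

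**The concern.** The participants are school students, and suicidal ideation is the primary research question. Staff who follow one section would wait for a parent's consent before speaking to that parent about a result. Staff who follow another would speak to the parent and wait for consent only before referring. Taken literally, the first rule asks parents to agree before they are told what the matter is. The two definitions of severe ideation can give the same answer sheet different labels, and the article says that students in the severe band often need immediate help.

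The second issue is inferential. The baseline assessment can itself lead to counseling for the students with most room to improve, and that counseling can fall between baseline and the 8-week measurement. With a single group, nothing in the data separates its effect from that of the two workshops.

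**Working it through.** No figure in the plan needs reproducing here. The check sets the sections side by side, tests the two severity definitions, and then illustrates the inferential point.

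**1. Disclosure and referral**

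| Section | Who | Consent before parents are told? | Consent before referral? |
|---|---|---|---|
| Consent for Publication | students whose results suggest susceptibility | yes | not stated separately |
| Potential Risk to Participants | students susceptible on their scores | no, sharing is stated as a fact | yes |
| Ancillary and Posttrial Care | identified cases, then extreme cases | not addressed | none stated |
| Data Monitoring and Management | anyone in distress | not addressed | none stated |

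The first two rows concern the same students and place the consent step at different points. That is a direct contradiction. The last two rows are silent on consent. None of *susceptible*, *identified* or *extreme* is tied to a score on the Modified Scale for Suicidal Ideation (MSSI).

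**2. Severity**

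For whole-number totals, 21 or higher and above 20 are the same threshold, so the conflict lies only in the added item condition.

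- Definition 1: total ≥ 21.
- Definition 2: total > 20 and item 7 > 1.
- Test case, 1 on each of 21 items: total = 21 × 1 = 21, item 7 = 1.
- Definition 1: 21 ≥ 21, severe. Definition 2: 21 > 20 holds but 1 > 1 fails, not severe.

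The students affected are those with a total of 21 or more and at most 1 on item 7. The documents do not allow that group to be counted.

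**3. Referral within the ideation change (illustration only)**

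Inputs from the article: 223 students (Sample Size, before the dropout allowance) and the 40% adolescent ideation rate cited in the Introduction. Assumptions: no programme effect, no new cases by 8 weeks, and some baseline cases resolved by referral alone. Lower prevalence is tried as well. With b resolved cases and no new ones, the exact two-sided McNemar p-value is 2 × 0.5^b. This is a simple stand-in for the planned model.

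| Baseline prevalence | Baseline cases | Resolved by referral | Prevalence at 8 weeks | p |
|---|---|---|---|---|
| 40% | 0.40 × 223 ≈ 89 | 9 | 80/223 = 35.9% | 0.004 |
| 20% (assumed) | 0.20 × 223 ≈ 45 | 9 | 36/223 = 16.1% | 0.004 |
| 10% (assumed) | 0.10 × 223 ≈ 22 | 4 | 18/223 = 8.1% | 0.125 |
| 10% (assumed) | 22 | 7 | 15/223 = 6.7% | 0.016 |

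Under these favorable assumptions a handful of resolved cases can be enough for a significant fall, though not in every scenario. Any new cases would weaken the result. The table shows what is possible and does not estimate what will happen in this trial.

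**The case against.** The consent named in Consent for Publication may be the written parental consent that every student needs to enroll (Inclusion Criteria; Recruitment, Step 3). If so, the condition is already met for everyone and the two sections agree on disclosure. The forms in Multimedia Appendices 2 and 3 may settle this, but they are not shown. The article does not say which consent it means, so the contradiction stands as written.

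A reader might infer that the article holds four incompatible referral rules. It does not go that far. Acute distress during data collection, the study's own counselor, and onward referral for assessment can be three tiers, and silence on consent does not deny it. What remains is that the tiers are not stated as such and their consent steps do not line up.

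A reader might also infer that the two severity definitions send the same student down different referral routes. No referral section uses the severe band, and the planned ideation model is binary, so the documents do not show that. The definitions still conflict.

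On inference, Strengths and Limitations already concedes the weakness of a design without a control group, and safeTALK itself aims to connect students with help. Help sought because of the workshop is fairly part of the programme. Referral triggered by the baseline assessment is a different matter, since it does not depend on attending a workshop. Model detail may sit in an analysis plan that is not shown, so silence in the article does not prove that referral will be ignored.

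**Conclusion.** Two contradictions hold on the text: where parental consent falls (before parents are told, or only before referral), and what counts as severe ideation. The counselor-referral sections add to the uncertainty because they state no consent step. These must be reconciled. Which rule applies is not a statistical question, and none is proposed here.

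The inferential point also holds, in limited form: the baseline-to-8-week change in ideation is the combined result of the programme, any referral, and whatever else changes over time in one uncontrolled group. It cannot be credited to RAAHI and safeTALK alone. The size of the referral share cannot be computed, because the article gives no referral rate and no counseling effect. The p-values above depend wholly on their assumptions.

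A reader might infer that students will report less ideation at later visits because scores reach parents. The documents do not support that: families learn of score sharing at consent and assent, before the baseline questionnaire, so any general deterrent would act at baseline too.

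**What to change.** - **Pathway and definition.** Before further data are collected, the investigators and the ethics committee should reconcile Suicidal Ideation, Data Monitoring and Management, Consent for Publication, Potential Risk to Participants, and Ancillary and Posttrial Care. The result should be one disclosure and referral pathway with one severity definition. It should state which group each step applies to and where consent falls, and be checked against the consent and assent forms.
- **Recording.** Record the date of any referral or counseling for each participant, and report the number referred.
- **Wording of the estimate.** Describe the ideation change as the effect of the programme plus referral, subject to the limits of a single-group design.
- **Any table by referral status** should be descriptive only. Referral would tend to select students with high baseline scores, who would be expected to improve through regression to the mean even without counseling. The table should carry that caveat and should not be used to isolate a programme effect.

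The cost is a short amendment, a check of the forms, one or two extra recorded fields, and a few lines in the report. The design and sample size do not change.

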### Potential Risk to Participants

This study has minimal potential risks for the participants. While obtaining informed consent from the parents and assent from the participants, it will be made clear that information regarding those considered susceptible, based on their scores, will be shared with their parents, and they will be referred for further assessment after the parents’ consent. However, the status of the participants will be kept confidential from the school authorities. The study will involve psychologists who will conduct the interview along with the principal investigator; hence, they will be able to screen the potential participants.

### Ancillary and Posttrial Care and Referral Mechanism

The data will be collected by trained psychologists, and all the identified cases will be referred to a counselor who will also be hired for the study, so they can refer the extreme cases for further treatment. The employed counselors will be on hand at the study sites for data collection and intervention. The cases presenting extreme suicidal ideation thoughts will be referred for follow-up. The screening and referral expenses of the participants will be borne by the study [71]. The attendees will also be informed about the resources that are accessible, such as the hotlines of the suicide prevention organizations operating in Pakistan.

For this trial, the criteria for discontinuing or modifying allocated interventions for a participant will include a participant’s explicit request to withdraw, the emergence of any unforeseen serious adverse events related to the intervention, or if the participant’s mental state significantly deteriorates, requiring a different level of care. Strategies to improve adherence to the intervention protocol will involve clear communication of the program’s duration and expectations during the informed consent process; regular engagement with participants, which may include follow-ups; and ensuring the intervention is delivered in a manner that is acceptable and feasible for the participants. Participants will be informed about any permitted or prohibited concomitant care or interventions during the trial period to avoid any potential confounding factors.

## Results

### Study Progress to Date

As of July 30, 2025, significant progress has been made in the initial phases of the project. This includes the successful acquisition of permissions from the AKU-ERC and relevant district education offices in GB and intervention development and validation. Furthermore, the pilot testing of the intervention materials was completed in October 2024, providing valuable insights for the main study. Currently, the recruitment of participants is underway and is scheduled to commence fully in August 2025. Importantly, funding for this project has already been confirmed through a grant from the Fogarty International Center at the National Institutes of Health.

### Projected Timeline

This project is proceeding according to the subsequently mentioned timeline, which outlines the key milestones and their anticipated completion dates. Participant recruitment is expected to be completed by July 2025, followed immediately by baseline assessments, also in July 2025. The intervention delivery period is scheduled to run from July 2025 to August 2025. Postintervention assessments will take place in September 2025. Data cleaning and analysis will commence immediately following the postintervention assessments. Subsequently, manuscript preparation will begin, and the final phase will involve dissemination activities to share the study findings.

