**Results:**

As of April 2025, 267 participants have been recruited from 2 of the 4 schools; data collection commenced in March 2025 and is projected to conclude in August 2025. Final results are expected to be published by February 2026.

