### Research Questions

The primary research question about suicidal ideation is as follows: What is the effect of suicide prevention programs (RAAHI and safeTALK) in reducing suicidal ideation among school-going adolescents in GB?

The secondary research question is as follows: What is the effect of suicide prevention programs (RAAHI and safeTALK) among school-going adolescents in GB on (1) perceived suicidal awareness; (2) perceived Social Support Questionnaire; (3) suicide literacy; (4) attitude toward seeking help related to suicidal ideation; (5) life attitude schedule; (6) depression, anxiety, and stress level; (7) adaptive coping strategies; and (8) self-efficacy.

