### Null Hypotheses

The hypotheses are as follows:

Hypothesis 1—suicidal ideation risk among school-going adolescents in GB is similar at baseline and 8 weeks following the implementation of the suicide prevention program.Hypothesis 2—Compared to baseline, there is no mean difference in suicide awareness, suicide literacy, and attitude to seek help after 8 weeks of participation in a suicide prevention program (RAAHI and safeTALK) among school-going adolescents.Hypothesis 3—Compared to baseline, there is no difference in the mean score of depression, adaptive coping strategies, and self-efficacy after 8-week suicide prevention programs (RAAHI and safeTALK) among school-going adolescents.

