#### Posttest Phase

The data will be recollected on all outcome measures during posttest phase 1, which is right after the intervention, and posttest phase 2, which will be after 8 weeks of the intervention (Figure 2).

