### Time Frame for Data Collection

Each participant will receive a short questionnaire at 3 points in time: pretest baseline data (T1), immediately after the intervention (T2), and 8 weeks after the intervention (T3). This self-filled questionnaire will collect data on suicidal ideation, level of suicide literacy, level of confidence, and openness to disclose suicidal ideas to others. The researcher will be responsible for checking for and verifying any missing data with participants, which will help to identify and correct errors in the datasets.

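### The projected timeline leaves no room for the 8-week assessment after any workshop held later than 5 August 2025, and the recruitment statements contradict one another

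*Protocol article*

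**What the plan says.** **The time point.** Under Research Questions, suicidal ideation is the primary question ("The primary research question about suicidal ideation is as follows"). Hypothesis 1 under Null Hypotheses states that "suicidal ideation risk among school-going adolescents in GB is similar at baseline and 8 weeks following the implementation" of the programme. Posttest Phase places a first posttest right after the intervention and a second, "posttest phase 2, which will be after 8 weeks of the intervention". Time Frame for Data Collection applies the same schedule to each participant: baseline (T1), then "immediately after the intervention (T2), and 8 weeks after the intervention (T3").

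**The calendar.** Under Projected Timeline, "The intervention delivery period is scheduled to run from July 2025 to August 2025" and "Postintervention assessments will take place in September 2025". Data cleaning and analysis follow at once. The abstract's Results paragraph instead has data collection running from March to August 2025. Study Phases gives 30 October 2025 as the end of the study.

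**Recruitment.**
- Abstract, Results: "As of April 2025, 267 participants have been recruited from 2 of the 4 schools".
- Study Progress to Date, as of 30 July 2025: "the recruitment of participants is underway and is scheduled to commence fully in August 2025".
- Projected Timeline: recruitment complete by July 2025, with baseline assessments in the same month.

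**The concern.** A single assessment month directly after a two-month delivery period cannot hold an 8-week follow-up for everyone. If the calendar were followed, students trained later in August would be assessed earlier than 8 weeks, yet their data would enter an analysis described as an 8-week comparison.

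This matters more here than in a controlled trial. There is no comparison group, and Study Design and Sampling Strategy rest the causal argument on repeated assessments at known times relative to the intervention. If elapsed time differs between workshop groups, the estimated change from T1 to T3 no longer refers to one defined interval.

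The recruitment statements matter for a related reason. The figure of 267 is the full target after the dropout allowance (Sample Size), and the design has four schools. A reader cannot tell whether enrolment is finished, nor how many schools contribute data.

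**Working it through.** **Inputs.** T3 is 8 weeks = 56 days after the intervention (Posttest Phase; Time Frame for Data Collection). Delivery is July to August 2025, at the widest 1 July to 31 August, and assessments are in September 2025, 1 to 30 September (Projected Timeline). The abstract closes data collection in August 2025. The study ends on 30 October 2025 (Study Phases). No visit window is stated, so T3 is taken as exact.

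**Formula.** T3 date = workshop date + 56 days. Latest workshop date = closing date − 56 days.

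**Does September 2025 follow from the plan's own dates?**

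| Workshop | T3 | In September? |
|---|---|---|
| 1 July | 26 August | no, earlier |
| 7 July | 1 September | yes, first day |
| 5 August | 30 September | yes, last day |
| 6 August | 1 October | no, later |
| 31 August | 26 October | no, later |

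So September is not reproduced. Delivery from 1 July to 31 August implies T3 from 26 August to 26 October. Only workshops from 7 July to 5 August have an exact T3 within September.

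**Longest possible follow-up for the latest workshop.** 31 August to 30 September = 30 days, or 30/7 = 4.3 weeks, against the 8 weeks required.

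**Under the abstract's closing date.** 31 August − 56 days = 6 July, so only workshops in the first six days of July would allow an 8-week T3.

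**Under the study end.** 30 October − 56 days = 4 September. Delivery up to 31 August therefore fits the overall study period with exact-day assessment. With a window of plus 1 week, the last T3 window closes on 26 October + 7 days = 2 November, past the study end. To close by 30 October, the last workshop must be on 30 October − 63 days = 28 August.

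**Recruitment statements side by side.** All 267 recruited by April 2025; complete by July 2025; still to begin in full in August 2025 according to a report dated 30 July. Full recruitment by April is incompatible with recruitment that on 30 July has yet to begin in full, and so is completion by July.

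**The case against.** **The design text is sound.** The hypothesis, the posttest description and the data collection schedule all agree on 8 weeks, and the last of these applies it to each participant. The timeline is a month-level projection, and the stated study end accommodates an 8-week T3 after a 31 August workshop. This stands. It makes the problem an error in the schedule, not a faulty choice of endpoint or time point.

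**The September assessments might mean T2 only.** This does not help. T2 is due right after each July or August workshop, and T3 would then have no place before analysis begins.

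**Stronger readings that the documents do not support.**
- A reader might infer follow-up ranging from 1 day to 13 weeks. That assumes everyone is assessed in September whatever the workshop date, which is nowhere stated. The upper end also needs a 1 July workshop, which sits badly with recruitment and baseline taking place in July.
- A reader might infer that about 42% of students are affected, since 26 of the 62 days from 1 July to 31 August fall after 5 August. That assumes workshops spread evenly over calendar days. With about 30 students per workshop, 267 students make roughly nine groups (267/30 = 8.9), and none is dated. The true share could be smaller or much larger.
- A reader might infer that only two schools are in the study. This rests on one sentence in the abstract. The Methods and the limitations state four schools, and the progress report contradicts the premise that enrolment is complete. A reporting error is equally possible.
- A reader might infer bias in favour of the programme, or confounding with school. The first requires effects that fade, for which the article gives no figure for this programme; the second requires an order of schools, which it does not give.

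**Conclusion.** The point holds as a contradiction between the schedule and the primary time point. On the stated dates, an exact 8-week T3 by 30 September is impossible for any workshop after 5 August 2025, and a 31 August workshop allows at most 30 days. The abstract's August close would move the cut-off back to 6 July. These dates assume an exact 56-day interval; a short tolerance would shift them by days but would not accommodate late-August workshops.

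The number of students affected cannot be derived. Nor does the article show that T3 was or will be mistimed: it shows that following the published calendar would mistime it.

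The recruitment statements conflict, and the number of contributing schools is left unclear; a change to a two-school design is not shown.

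The correction should be made, but it is less than a critical flaw: the definition of T3 is consistent throughout, and the fault lies in the timeline and status text.

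**What to change.** 1. Correct Projected Timeline and the abstract so that T3 follows each workshop by 8 weeks: 26 August to 26 October 2025 for delivery from 1 July to 31 August. Start the analysis only after the last T3.
2. If a visit window is used, make it close by 30 October 2025 or move the study end. A window of plus 1 week requires the last workshop by 28 August. If delivery runs past 4 September, which is possible if recruitment begins in full only in August, the study end must move even for exact-day assessment.
3. Record the actual number of days from workshop to T3 for every student.
4. Replace the statements in the abstract, Study Progress to Date and Projected Timeline with one dated recruitment statement giving enrolment by school, and say whether all four schools contribute.

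**Cost.** This needs changes to wording and calendar. Data collection ends on 26 October instead of 30 September, 26 days or about 4 weeks later, and analysis starts correspondingly later. Neither the outcome nor the hypothesis changes.
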